### Statistical analysis

#### Primary outcome

The effect of the implementation strategies on lower-SES participation will be analysed using mixed-effects logistic regression models. This analysis technique allows for the clustering of patients within primary care practices, for dependence of observations within individuals over time, and provides intention-to-treat analysis as required by the Consolidated Standards of Reporting Trials (CONSORT) Statement. The allocated implementation strategy will be used as the fixed between-groups factor.

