##### SES-sensitive implementation strategy

The SES-sensitive implementation strategy will encompass all the topics described in the regular implementation strategy, but will be tailored to match the needs of the lower-SES target group.

The GP nurses will receive a 3-h training (instead of a 2-h training), and follow-up meeting of 1.5 h (approximately 2 months after the training visit) in which extra elements of the SES-sensitive implementation strategy will be addressed. This additional section of the training was developed in collaboration with a representative of the Dutch Centre of Expertise on Health Disparities (Pharos). An important component is the recognition and guidance of lower-SES patients who might benefit from the online CDMIs. GP nurses will be taught about the concept and consequences of health-literacy skills and ways to recognise and align with the needs of patients with a lower SES or low/limited health-literacy skills. They will practice with methods to provide support to patients with lower SES or health-literacy skills (e.g. easier language and communication, teach-back method). They will also be strongly advised to provide a more directive approach to guiding patients and encouraging them to use the CDMIs. Practical tips will be given to do this, such as: not immediately offering the online CDMIs during the first visit, but after trust and alliance have been established, seeking contact more often (face-to-face, by telephone or monitoring system) to provide guidance, helping patients create an account, indicating which exercises the patient should do (an overview of exercises and suggestions is given in the manual), doing the online exercises with patients during face-to-face sessions before doing them alone (modelling), focussing on one or a few exercises to reduce the chance of experiencing failure, using appropriate language and checking whether information is understood (e.g. using the teach-back method).

The GP nurses in this condition will also have access to a helpdesk service, at least two implementation team meetings and ongoing communication activities from the research teams, but special attention will be paid to the lower-SES target group in all these actions.

Additional elements of the SES-sensitive implementation strategy aimed at the patients are:

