### Outcome measures

#### Primary outcome

The (difference in the) participation rate of patients with a lower SES in the CDMIs is the primary outcome. Participation is defined as participating in at least one face-to-face session with a GP nurse (as registered by the GP nurse) and engaging with at least two exercises in the online CDMIs (as determined with the user data of the online CDMIs). It is hypothesised that in the SES-sensitive implementation strategy arm of the trial the participation rate of lower-SES patients will be significantly higher than in the regular implementation strategy arm. This outcome requires an operational definition of SES, but SES can be defined in various ways. Indicators that are commonly used are education, income and work status/occupation [31–35]. Education is a widely used indicator, especially in the Netherlands, and has some advantages over the other two indicators [36–38]. First, the level of education is generally stable after early adulthood, whereas work status and level of income fluctuate more. Second, in general, respondents are willing to report their level of education, while respondents might be unwilling to disclose or even misstate the level of their income [38, 39]. For these reasons, education will be the main indicator of lower SES in this study. In addition to education level, income, work status and status level of the neighbourhood will be taken into account because these indicators cover different dimensions of SES and are, although interrelated, not interchangeable with education [33, 34].

Therefore, in this study, a lower SES will be defined as:
The highest completed educational level is intermediate vocational education (i.e. between lower and higher vocational education, in Dutch: MBO in Dutch: MBO) or lower, and/orThe respondent is unemployed (looking for work) and lives in a neighbourhood with a negative status level score, and/or:The total gross family income of the respondent is below the social minimum income in the Netherlands (per July 2017), and lives in a neighbourhood with a negative status score

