Self-reported education will be assessed with a single item (What is your highest completed educational level?) with eight response options: none/primary school, lower vocational education, intermediate secondary education, higher secondary education, intermediate vocational education, higher vocational education, academic education, and other type of education. We use the term ‘lower SES’ in this study as we include intermediate levels of education in our definition of lower SES. In the Netherlands, four levels of intermediate vocational education are discerned. Persons who report an intermediate vocational education as their highest completed education level will be asked to indicate which type of intermediate vocational education they completed (answer options correspond to the four levels). Generally, the first level is used as the cut-off for highest completed educational level in a low-SES definition (e.g. by Statistics Netherlands). However, we use the fourth level as the cut-off for highest completed educational level. We chose a higher cut-off point because it is mainly the highly educated (i.e. higher vocational education and academic education) that are currently reached with e-health interventions, despite the risk of depression generally increasing as educational level decreases [8].

Self-reported gross family income will be assessed with a single item. In the Netherlands, the social minimum income is dependent upon living arrangements (persons who live alone or as a single parent: rounded to an average of €1100 for this study, and for persons with any other type of living arrangement: €1550) which is reflected in the answer options: more or less than €1100 or more or less than €1550. Self-reported work status will be assessed with a single item using the following answer options: employed/self-employed, unemployed, occupationally disabled, student, volunteer work, retired, homemaker. Status level scores of the neighbourhood will be assessed by asking respondents their four-digit zip code. The Netherlands Institute for Social Research provides status scores for every zip code. For this study, the status level scores of 2016 will be used. A negative status level score indicates a lower than the Dutch average status level score of the years 1998–2016.

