### Sample size calculation

The sample size is based on the main outcome, namely participation rate of patients with a lower SES. This is defined as participating in at least one face-to-face session with a GP nurse and completing two exercises in the online CDMIs (see above). We expect a (base) participation rate of 18% with the regular implementation strategy. Due to a paucity of studies about online psychological interventions offered and guided by primary care professionals, this percentage is based on previous (baseline) participation rates of lower-educated people in studies of online self-help interventions for depression [18, 20]. This percentage also takes into account that our definition of participation entails more than just starting with the intervention/trial and that attrition in e-health can be related to indicators of lower SES [9]. We aim to double the participation rate of lower-SES patients to 36% by using the SES-sensitive implementation strategy; a smaller effect was not deemed to be relevant. As far as we know, there is no empirical evidence that might support this doubling; however, our rationale is that with specific training and specific materials this percentage of participating lower-SES patients can be reached. The difference between these fractions (0.18 vs. 0.36) will be tested at a two-sided significance level of 5% and a power of 80%. Accounting for the clustering in the data with six patients on average per GP nurse (range 2–14 patients) and an intraclass correlation of 0.02, we need *n* = 114 patients in each condition (in 19 GP nurses per condition) or 228 participants in total. This normative sample size calculation was performed in Stata version 14.2 statistical software package using the clustersampsi-procedure, taking into account the mean cluster size, cluster size variation and the intraclass correlation [53]. The intraclass correlation value of 0.02 was based on the Hospital Anxiety and Depression Scale (HADS)-depression scores in the primary care setting as reported by Adams and colleagues (2004), Table 5 [54].

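### The primary model names only the allocated strategy, although recruitment after nurse randomisation can leave patient education unbalanced within the broad lower-SES group; education should be a prespecified covariate

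*Protocol article*

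**What the plan says.** **Model.** Under Statistical analysis, Primary outcome, the article sets out a mixed-effects logistic regression that allows for clustering. The only fixed effect named is treatment: "The allocated implementation strategy will be used as the fixed between-groups factor". No patient-level covariate is named there, and Additional analyses describes no education-adjusted analysis of the primary outcome.

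**Population.** Under Outcome measures, Primary outcome, the education route into lower SES starts at none/primary school, and its upper limit is set deliberately high: "However, we use the fourth level as the cut-off for highest completed educational level". Two further routes, unemployment or a family income below the social minimum, each combined with a negative-status neighbourhood, admit patients whatever their education.

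**Recruitment.** Nurses know their allocation (Design) and recruit by the strategy assigned to them (Eligibility criteria and recruitment, GP nurses). Of the extra training in one arm the article says: "An important component is the recognition and guidance of lower-SES patients who might benefit from the online CDMIs". Randomisation is stratified by the SES of the neighbourhood where the nurse works (Randomisation), not by anything measured on patients.

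**Outcome gradient.** The sample size section accepts that "attrition in e-health can be related to indicators of lower SES". In choosing education as the main SES indicator, the article notes that "the level of education is generally stable after early adulthood".

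**The concern.** In a cluster trial where patients enter after allocation, through staff who know the allocation, randomisation protects the comparison of nurses but not the mix of patients each arm brings in. Here differential recruitment is close to being the purpose of the intervention: one arm is taught to find and engage patients whom the other arm may overlook.

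The lower-SES group is wide enough for this to matter. Someone with primary school only and someone with MBO level 4 count alike, and they may differ in how readily they reach one consultation and two online exercises. If the arms differ in that mix, a model with strategy alone attributes the difference to the strategy. A strategy that succeeded in reaching the least educated could then look weaker than it is, and a true doubling could be reported as non-significant. If instead the SES-sensitive arm enrolled patients who were easier to engage, its effect would be overstated.

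**Working it through.** **1. The plan's own figure.** Inputs from Sample size calculation: 18% against 36%, two-sided 5%, 80% power, mean cluster size 6 (range 2-14), ICC 0.02, stated result 114 per arm in 19 nurses.

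- Without clustering, pooled two-proportion formula: n = [1.96·√(2·0.27·0.73) + 0.842·√(0.18·0.82 + 0.36·0.64)]² / 0.18² = 94.3, so 95 per arm.
- The coefficient of variation (CV) of cluster size is not stated. Range/4 gives SD = 12/4 = 3, so CV = 3/6 = 0.5 (assumption). Design effect = 1 + [(1 + 0.5²)·6 − 1]·0.02 = 1.13.
- 95 × 1.13 = 107.4, or 18 nurses. With a t-based power calculation, 18 nurses give 79.4% and 19 give 81.6%. So 19 × 6 = 114.

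The stated figure reproduces, and there is little reserve above 80%.

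**2. What a shift in education mix does to the expected difference.** The article gives neither an education gradient within lower SES nor an expected imbalance, so both are assumed. Take two education bands, half the regular arm in each, and a participation odds ratio of 2 for upper against lower band.

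- Regular arm: 13.0% (lower) and 23.0% (upper). Overall 0.5·13.0 + 0.5·23.0 = 18%.
- To reach 36% with the same mix, the within-band strategy odds ratio is 2.62, giving 28.1% and 43.9%.
- SES-sensitive arm with 10 points more in the lower band: 0.6·28.1 + 0.4·43.9 = 34.4%. Difference 16.4 points.
- 20 points more: 0.7·28.1 + 0.3·43.9 = 32.8%. Difference 14.8 points.
- 10 points fewer: 0.4·28.1 + 0.6·43.9 = 37.6%. Difference 19.6 points.
- No true effect, 20 points more: 0.7·13.0 + 0.3·23.0 = 16.0%. Difference −2.0 points.

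With 30-50% of the regular arm in the lower band, an excess of 10-20 points leaves about 16-17 of the 18 points at an education odds ratio of 1.5, about 15-16 at 2 and about 13-16 at 3. A reverse imbalance of 10 points gives about 19 to 20.5.

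**3. Power and estimates by simulation.** 38 nurses of 6 patients, ICC 0.02, 40% lower band in the regular arm, 600 runs per scenario, logistic regression with nurse-clustered standard errors:

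| Education OR | Shift (points) | True OR | Unadjusted OR / power | Adjusted OR / power |
|---|---|---|---|---|
| 1.5 | 0 | 2.58 | 2.58 / 83% | 2.61 / 83% |
| 1.5 | +10 | 2.58 | 2.46 / 79% | 2.59 / 82% |
| 1.5 | +20 | 2.58 | 2.33 / 74% | 2.56 / 79% |
| 2 | +10 | 2.61 | 2.39 / 76% | 2.61 / 82% |
| 2 | +20 | 2.61 | 2.36 / 72% | 2.79 / 83% |
| 3 | 0 | 2.68 | 2.58 / 84% | 2.72 / 86% |
| 3 | +10 | 2.68 | 2.33 / 74% | 2.73 / 84% |
| 3 | +20 | 2.68 | 2.06 / 60% | 2.66 / 82% |
| 3 | −10 | 2.68 | 2.87 / 90% | 2.73 / 86% |

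With no true effect and a 20-point shift, the unadjusted odds ratio is 0.86 (education OR 2) or 0.80 (education OR 3), with 8-9% false positives; adjusted, it is 0.98-0.99 with 4-5%.

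**4. A second set of assumptions.** Three bands, regular-arm participation 24/16/8% or a flatter 21/16/12%, mix 50/30/20%, clusters of 2-14, 1,500 runs. Equal mix: 78-81% unadjusted, 81% adjusted. With 10 points moved from top to bottom band: 67-74% against 79%. With 20 points: 53-64% against 76-78%.

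Both simulations used cluster-robust logistic regression, not the planned mixed model, so the figures are indicative.

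**The case against.** **An article need not list covariates.** It does not say that allocation is the only covariate, and an analysis plan not shown could add others. That is fair, and silence should not be read as exclusion. But the article does state a primary model, and that model does not fit the recruitment process it describes.

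**Direction.** A reader might infer that the bias runs towards no difference. The documents do not establish this. The training concerns lower SES and limited health literacy in general; that it reaches the lowest end of the group is an inference. The same section advises offering the modules only once trust has been built, which could select more engaged patients and inflate the effect. With no true effect, a shift towards the least educated makes the strategy look harmful, which is away from no difference. The remark on attrition in the sample size section gives no gradient within lower SES.

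**Size.** Gradient, mix and shift are all assumed. A modest imbalance costs about 1-3 of the 18 points, and with equal mix adjustment gains almost nothing. This stands.

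**Planned analyses.** Additional analyses includes a lower education cut-off and a health-literacy interaction. These partly expose the problem, but the first changes who is analysed and the second is exploratory; neither adjusts the primary estimate.

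**Limits of adjustment.** Education is recorded only after consent, account creation and first login (Inclusion procedure), so it is unknown for patients who stop earlier. Motivation and alliance remain uncontrolled. Under Aim, the hypothesis concerns the percentage of lower-SES participants, and Additional analyses speaks of SES as the outcome; on that reading education helps define the outcome and adjusting for it would be invalid. All of this stands and limits the fix.

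**Conclusion.** The point holds as a design-based weakness of the stated primary model, not as a demonstrated bias. Post-randomisation recruitment by unblinded nurses, recognition training in one arm and stratification on a nurse-level factor mean that nothing in the design balances patient education within the lower-SES group. If education predicts participation there, the unadjusted effect is biased, in a direction that depends on whom the SES-sensitive arm enrols.

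Under the assumed gradients, a 10-20 point shift towards the least educated takes power from about 80% to roughly 50-75%; the shallowest gradient with a 10-point shift leaves 79%. Adjustment brings it back to about 76-84%. A reverse shift of 10 points raises the odds ratio to 2.72-2.87, against true values of 2.58-2.68. None of these magnitudes comes from the documents.

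The conclusion is confined to the primary outcome read as the participation rate among lower-SES patients, as in Outcome measures and Sample size calculation. It should be acted on because the variable is already collected and adjustment costs little; confidence is medium.

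**What to change.** Under Statistical analysis, Primary outcome, for the participation rate among lower-SES patients:

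- Prespecify highest completed education as a patient-level fixed effect. The bands must place every analysed patient, including those answering other type of education and those with higher vocational or academic education who qualify through the unemployment or income routes.
- Keep the model without education as a sensitivity analysis, and tabulate the education mix of the lower-SES group by arm.
- Report a standardised risk difference beside the odds ratio, to be read against 18% and 36%.
- State that the adjustment removes only measured case-mix.
- State that it does not apply if the outcome is the lower-SES share of participants.

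Age need not be added on these grounds; nothing in the documents or calculations supports it here.

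The cost is analysis-plan wording, a few extra parameters, and an odds ratio that becomes conditional on education, which is why the standardised risk difference should accompany it.

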#### Secondary outcomes

##### Impact on complaints and well-being

Linear mixed models will also be used to analyse the impact of the implementation strategies on the (secondary) psychological complaint outcomes (i.e. depression, sleep, stress, worry and anxiety) and well-being. In this instance our interest is not in comparing between-group differences on complaint-related outcomes, as both groups will receive the online CDMI intervention (albeit with a different type of implementation strategy). However, we are interested in examining whether there are within-group differences in clinical outcomes (i.e. reductions in complaints) between baseline and follow-up, especially in the SES-sensitive implementation group. For this purpose, growth curve analysis will be performed to examine the within-group trajectories of the complaint-related outcomes. Again, clustering will be accounted for in these analyses.

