### Design

A pragmatic cluster randomised controlled trial with two parallel groups will be conducted in which the two implementation strategies will be compared. As the GP nurse plays a key role in the implementation strategies, randomisation will take place at the level of the GP nurse in order to avoid contamination between the two implementation strategy conditions. Thus, each GP nurse will be randomised to one of the two implementation strategy groups. GP nurses cannot be blinded to the implementation strategy that they are allocated to because they will be aware whether their allocated implementation comprises specific components aimed at reaching lower-SES patients. The randomisation status will not be disclosed to patients. It is worth noting that the online CDMIs will be implemented in both conditions, meaning that the intervention will not be withheld from any patients participating in the study. Moreover, patients are free to receive any other type of care during the study. Participating patients will be assessed at baseline (T0), 3 months after baseline (T1) and 12 months after baseline (T2). Assessments among participating GP nurses will take place at two time points: at baseline, and 6 months after baseline. See Fig. 1 for the flowchart of the study and Table 1 for an overview of the schedule of enrolment, interventions and assessments in accordance with the SPIRIT Statement. This study is registered at the Netherlands Trial Register (NL6595) and was approved by the Medical Ethics Committee of the VU University Medical Center.

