#### Additional factors

##### Sociodemographic factors

In addition to income, work status and neighbourhood status (see above), other sociodemographic factors that will be assessed are: age, gender (male/female), living arrangement (alone, with partner, with partner and children, without partner and with children, with parents, other), marital status (single, married, civil partnership, divorced, widowed) and country of birth.

Data will be assessed in all patients, not only lower-SES patients. First, secondary outcomes (such as impact on complaints and well-being) will primarily be examined for within-group differences, but we are also interested in between-group differences. Second, because ‘low SES’ and ‘participation’ can be defined in various ways we will conduct additional analyses for which data from all patients are needed. Lastly, in order to compare outcomes with other studies, secondary outcomes of all patients must be assessed.

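### The complaint and well-being analysis is meant to show the impact of the strategies but rests on uncontrolled within-arm change, and two sections disagree on whether the arms will be compared

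*Protocol article*

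**What the plan says.** All of this is in the protocol article.

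- *Impact on complaints and well-being* opens by saying that linear mixed models will "analyse the impact of the implementation strategies on the (secondary) psychological complaint outcomes" and well-being. The next sentence reads "In this instance our interest is not in comparing between-group differences on complaint-related outcomes", the reason given being that both groups receive the online CDMIs.
- The same section then states what is of interest: "within-group differences in clinical outcomes (i.e. reductions in complaints) between baseline and follow-up, especially in the SES-sensitive implementation group". The method is that "growth curve analysis will be performed to examine the within-group trajectories of the complaint-related outcomes", with clustering accounted for.
- *Sociodemographic factors*, in explaining why data are collected from all patients, says the secondary outcomes "will primarily be examined for within-group differences, but we are also interested in between-group differences".
- *Patients*, under eligibility, requires current worry, stress or sleep problems and sets no score threshold.
- *Design* states that both arms implement the CDMIs and that "patients are free to receive any other type of care during the study". Patients are assessed at baseline, 3 months and 12 months.

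**The concern.** There are two linked problems.

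First, the question and the analysis do not match. The strategies are what is randomised, so their impact on complaints is a difference between arms. The section names that impact as its object and then sets the difference aside. That both arms receive the CDMIs is a reason to expect a small difference. It does not make within-arm change a measure of the strategies, because a CDMI effect would appear in both arms.

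Second, the two sections disagree on whether a between-arm comparison is of interest. That decides whether a reader should treat such a result as planned or post hoc.

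At stake is the reading of six secondary outcomes: depression, sleep, stress, worry, anxiety and well-being. A fall in complaints in the SES-sensitive arm, which the plan singles out, could be taken as an effect of that strategy when nothing in the analysis separates it from the other causes of change.

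**Working it through.** **1. The sections side by side.** Both put the within-group analysis first. They conflict on one point only: *Impact on complaints and well-being* disclaims an interest in between-group differences that *Sociodemographic factors* declares.

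**2. What within-arm change contains.** Patients are selected for current complaints (regression to the mean, natural recovery), other care is free (other treatment), and both arms get the CDMIs (any CDMI effect). No arm goes without the CDMIs, and the article describes no way to separate these parts.

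**3. The plan's figure used below.** The article gives no figure for the complaint analysis. The only number borrowed is 114 per arm from *Sample size calculation*. It reproduces:

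- 0.18 vs 0.36, two-sided 5%, 80% power: (1.96·√(2·0.27·0.73) + 0.842·√(0.18·0.82 + 0.36·0.64))² / 0.18² = 94.3, so 95 per arm.
- Design effect 1 + ((1 + CV²)·6 − 1)·0.02. Reading the range 2–14 as uniform (an assumption) gives CV 0.577 and a design effect of 1.14.
- 95 × 1.14 = 108.3, so 109; 109/6 rounds up to 19 nurses; 19 × 6 = 114.

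This does not bear on the concern. It only supplies n.

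**4. Illustration: change in one arm with no effect of anything.** Assumed, since the documents give neither: k, the baseline elevation above the patient population's long-run mean in SD, and ρ, the test-retest correlation. Also assumed: all 114 are followed up, the plan's ICC of 0.02 applies to change scores, and CV is 0.5, giving a design effect of 1 + (1.25·6 − 1)·0.02 = 1.13.

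- Expected change = k(1 − ρ) SD
- SE of mean change = √(2(1 − ρ))·√(1.13/114)
- With z = expected change / SE, P(significant) = Φ(z − 1.96) + Φ(−z − 1.96)

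Example with k = 0.5 and ρ = 0.6: change 0.20 SD; SE = 0.894 × 0.0996 = 0.089; z = 2.25; P ≈ 61%.

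| k (SD) | ρ = 0.5 | ρ = 0.6 | ρ = 0.7 | ρ = 0.8 |
|---|---|---|---|---|
| 0.25 | 24.1% | 20.2% | 16.3% | 12.5% |
| 0.50 | 70.9% | 61.3% | 49.4% | 35.5% |
| 0.75 | 96.5% | 92.1% | 83.1% | 66.4% |
| 1.00 | 99.9% | 99.4% | 97.3% | 88.8% |

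If only 57 per arm were followed up (mean cluster 3, design effect 1.055), the same grid runs from about 9% to 96%.

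**5. The same null, between arms.** A simulation of 4,000 trials (k = 0.5, ρ = 0.6, 19 clusters of 6 per arm, test on cluster means) gave significant improvement within one arm in 58% of runs. The between-arm test was significant in 4.9%, against a nominal 5%. That rate presumes that both arms enrol similar patients.

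**The case against.** The strongest reply is that the article poses a within-group question openly and gives its reason, and that its abstract frames the secondary objective as following complaints over time, which trajectories do. That stands as a defence of reporting trajectories. It does not cover the opening sentence of the section, which promises the impact of the strategies.

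A reader might also infer more than the documents support:

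- **That improvement with no effect is certain.** Entry is by experienced complaints, not a score cut-off, so regression to the mean could be small. Depression, anxiety and well-being are selected only indirectly and may regress less. Improvement is the expected direction, and its size is unknown.
- **That the between-arm comparison is left out.** *Sociodemographic factors* declares it, in second place. The fault is the inconsistency.
- **That the arms will be judged by which one reaches significance, or by a long list of separate tests.** No such comparison is planned. The article specifies growth curves and fixes no count of tests.
- **That the between-arm contrast is free of confounding.** Nurses are randomised, cannot be blinded, and then recruit patients under the assigned strategy. The SES-sensitive strategy is meant to change who takes part, and it advises against offering the CDMIs straight away at a first visit. The arms may differ in who enters and in when baseline is measured, and baseline adjustment may not remove this. The contrast is based on the randomised groups, which within-arm change is not, but it needs this caveat.

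**Conclusion.** The concern holds in limited form. Within-arm change from baseline cannot show an impact of the implementation strategies, and it does not isolate a CDMI effect either. The two sections contradict each other on whether between-arm differences are of interest.

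The size cannot be taken from the documents. Under the stated assumptions, the chance of a significant change in one arm with no effect at all is about 13% to 99.9%. The range is wide because it depends almost wholly on the assumed baseline elevation and test-retest correlation. It shows that a significant within-arm change would be weak evidence. It does not predict what the trial will find.

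These are secondary outcomes. The primary analysis and the sample size are untouched, so the change is advisable rather than critical.

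**What to change.** 1. Make *Impact on complaints and well-being* and *Sociodemographic factors* agree that the arms will be compared on these outcomes.
2. In the planned mixed models, include arm-by-time (3 and 12 months), baseline score and the neighbourhood-SES stratum. Add a GP-nurse random effect, and a patient random effect or residual covariance for the repeated scores.
3. Report the between-arm difference at each follow-up with its 95% CI as the result on impact of the strategies. State beside it that unblinded nurses recruit patients after randomisation, so the arms may differ at entry.
4. Keep the within-arm growth curves, labelled descriptive and uncontrolled, and do not describe them as impact of the strategies.

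Cost: a little more analysis work and one caveat in the report. No new data are needed, because the scores are already to be collected from all patients in both arms and mixed models with clustering are already planned.
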